**Figure 3 F3:**
[figure not shown]
**Visual presentation of reaction and response times in Matlab R2011b. (a)** Visual presentation of Backwards Digit Span task – green = stimulus that is heard by the patient, blue = answer of the patient; **(b)** Visual presentation of Stroop task. Since four stimuli per fragment are given, four reaction times per fragment can be calculated – green = stimulus that is heard by the patient, blue = answer of the patient.

The custom-made mobile phone task is a combined motor and cognitive task, in which the patients will have to type the test date (8 numbers) into a large-buttoned mobile phone (Emporia Talk Premium; Austria) (see Figure 2d). The number of errors and the time it takes to complete this task will be measured. The task is an untrained DT and tests recall and working memory as well as fine motor skills.

### Falls monitoring

For the entire study period of 24 weeks, the patient will receive a weekly phone call to ask about any fall events in the previous week. In case of a fall, questions are asked about the consequences and specific circumstances in which the fall took place (Table 4). Individual fall records will be communicated to the therapist, to enable adaptation of treatment. If a worrying trend of an increased fall risk would occur as a result of the treatment, therapists are expected to adapt their treatment accordingly and report this to the safety board of the trial. In addition, therapists will record any falls that may occur during the intervention. If safety adaptations imply a reduction of the intensity of treatment or in essence will require a change from an integrated to a consecutive training, patients will be considered to become a dropout and are included for the intention to treat analysis. The review board of the trial will have a six-monthly meeting in which the global fall rates will be monitored and discussed. A-priori fall rate increases as cutoffs for trial cessation will not be determined as falling can be very variable in PD and fluctuate according to medication status.

**Table 4 T4:** Weekly follow-up of falling

**In case of a fall:**	
**Description of fall**	When did you fall?
	At what time of the day?
	Can you describe what happened at the moment you fell?
	What were you doing?
	What was the cause of the fall?
	Where did you fall (inside or outside)?
**Medication**	When was the last time before the fall that you took medication?
	Was this medication still working (on or off)?
**Freezing**	Did freezing occur at the time of the fall?
**Dual tasking**	Were your hands free at the time of the fall?
	Were you talking to someone at the time of the fall?
**Adverse aspects related to fall**	Did you have any injury related to the fall?
	Are you more afraid of falling?

### Data analysis/statistics

A statistical analysis plan will be developed prior to unblinding and analysis. The primary data analysis will be performed according to an intention to treat principle. The primary endpoint, the DT walking performance at test session 1, 2, 3 and 4 will be evaluated using a linear mixed model. Tests will be two-sided with α 0.05. The fixed factors will be treatment (IDT vs. CTT), test session (1, 2, 3 and 4) and the interaction between test session and treatment group. Subject will be a random factor. The treatment difference will then be estimated by the appropriate contrast for the difference between the mean scores at test session 1, 2, 3 and 4. Secondary endpoints will be analyzed in a similar way. As a secondary question we will also model the three-way interaction between subgroup, i.e. those with and without freezing of gait (defined as a score of 1 on the New FOGQ), treatment group and time. Fall frequency data will be analyzed using a negative binomial model depending on the distribution of the data.

The influence of center, disease severity (Hoehn and Yahr scores) and cognition will be explored by including the interaction terms between treatment and each of these variables in the model. Throughout, 95% confidence intervals will be determined. Sensitivity analyses will be carried out to evaluate the impact of missing values on the outcome.

In addition descriptive statistics will be presented by means and standard deviations, as appropriate. When data are skewed, medians and quartiles will be calculated and for categorical data, frequencies and percentages will be presented.

Data will be analyzed using the data analysis software package IBM SPSS Statistics (version 19).

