### Randomization and blinding

Subjects will be randomly assigned per center to the earlier described integrated dual task (IDT) or consecutive task training (CTT). A computerized block randomization procedure will be implemented by an independent statistician using a block size of four subjects. Group allocation will be performed by an independent person, who will notify the treating physiotherapist by email to ensure concealed allocation. Randomization will be stratified by subgroup with or without FOG and by stage of the disease (Hoehn & Yahr stage II and III). To avoid bias, patients are assessed by blinded testers. In addition, participants will be explicitly instructed not to reveal any details about their training regime during testing to prevent unblinding. Both therapists and patients will be explained that both arms of the study are likely to be effective in improving dual task performance to control for expectancy effects, in line with the above outlined rationale for each training approach.

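### The primary model leaves out the three randomisation stratifiers (centre, freezing of gait, Hoehn & Yahr stage); adding them by session is a nearly free gain in precision to the extent that they predict the analysed contrast

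*Protocol article*

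**What the plan says.** On the design, the Protocol article (Randomization and blinding) states: "Subjects will be randomly assigned per center", and further: "Randomization will be stratified by subgroup with or without FOG and by stage of the disease", the stages being II and III. Allocation is in blocks, "using a block size of four subjects". Two centres, two FOG groups and two stages give 2 × 2 × 2 = 8 strata.

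On the analysis, the Data analysis/statistics section states: "The fixed factors will be treatment (IDT vs. CTT), test session (1, 2, 3 and 4) and the interaction", meaning that of session with treatment. It adds: "Subject will be a random factor". How the treatment effect is obtained is described in general terms only: "The treatment difference will then be estimated by the appropriate contrast for the difference between the mean scores at test session 1, 2, 3 and", the list closing with the fourth session. The other endpoints are to be handled alike.

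The stratifiers do appear in that section, but outside the primary model. FOG enters a secondary three-way interaction with treatment and time. Centre and Hoehn & Yahr score enter exploratory models through their interactions with treatment.

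**The concern.** Stratified allocation balances the arms on the stratifiers, so the variation these factors cause no longer adds to the chance difference between arms. An analysis that omits them can still count that variation as error. The estimated standard error is then larger than the true sampling variability, confidence intervals are too wide and the test rejects less often than its nominal 5%.

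The article gives some reason to expect this for FOG. The Background reports that freezers learned a serial reaction time task less well, and the Discussion says that they learn less well in dual-task conditions. Both statements concern learning, that is, change over sessions, and not only gait speed at entry.

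The question is whether the effect reaches the contrast that this particular model will estimate, and how large it could be.

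**Working it through.** **1. The plan's own sample size.** Inputs from the Sample size section: mean 0.77 m/s, SD 0.21, difference 15%, power 80%, two-sided 5%.
- Difference: 0.15 × 0.77 = 0.1155 m/s.
- Normal formula: n per arm = 2 × (1.96 + 0.8416)² × 0.21² / 0.1155² = 51.9, so 52 per arm (104 in total). The t-test version gives 52.9, so 53 per arm (106 in total). The stated 108 is close to both.
- Power with 54 per arm: 81.5% (normal) or 80.8% (t).

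This calculation uses the unadjusted SD and no covariates, so the planned power does not rely on adjusting for the stratifiers.

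**2. Stratifier main effects in the stated model.** The stated model was simulated with and without main effects of centre, FOG and Hoehn & Yahr stage. The setting was 120 patients and blocks of four in 8 strata, with 40 runs per scenario. Assumptions not in the documents: the strata explain 20% of total variance and the within-patient correlation is 0.7.

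| Contrast | Missing per post-training visit | SE ratio, adjusted / unadjusted |
|---|---|---|
| Change, session 3 vs 2, between arms | 0% | 1.0000 (SE 0.02945 in both) |
| Same | 5% | 0.9999 |
| Same | 10% | 0.9996 |
| Level at session 2, between arms | 0% | 0.90 |

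A stratifier's effect on level is the same at every session, goes into the subject effect and cancels from a within-patient change. Main effects alone therefore do nothing for a change contrast. They help only if the contrast compares the arms at a single session.

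**3. Stratifiers by session.** If the stratifiers explain a share R² of the variance of the analysed contrast, the SE ratio is √(1 − R²). The documents give no value for R², so the range is an assumption and includes zero. A simulation of a change outcome (120 patients, blocks of four in 8 strata, 8,000 runs per scenario) gave:

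| Assumed R² | √(1 − R²) | Simulated SE ratio | Type I error without / with stratifiers | Power without / with, at an effect with nominal 80% |
|---|---|---|---|---|
| 0% | 1.000 | 1.001 | not reported | 79.4% / 79.4% |
| 5% | 0.975 | 0.975 | 4.6% / 5.2% | 80.2% / 81.5% |
| 10% | 0.949 | 0.949 | 4.0% / 4.7% | 81.1% / 84.0% |
| 20% | 0.894 | 0.893 | 3.1% / 5.1% | 81.6% / 87.2% |

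The power gain is 81.5 − 80.2 = 1.3, 84.0 − 81.1 = 2.9 and 87.2 − 81.6 = 5.6 percentage points. It is modest because stratified allocation already keeps the arms balanced, whichever model is fitted.

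**4. Cost in parameters.** Three binary factors add 3 main effects. Each crossed with four sessions adds 3 more, so 3 × 3 = 9. The total is 3 + 9 = 12.

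**The case against.** The strongest reply is that the model already handles the problem. It has a random subject effect, so each patient serves as their own control, and stable baseline factors drop out of a change contrast. That is correct for effects on level, as step 2 shows. A reader might infer from the missing stratifiers that the standard error is simply too wide and that power is being thrown away. The documents do not support that: nothing in them says how far centre, FOG or Hoehn & Yahr stage predict change, and at R² = 0 nothing is lost.

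Second, the plan does not ignore the factors. The Discussion's specific prediction for freezers, that they may gain more from consecutive training, is effect modification, and the FOG-by-treatment-by-time model addresses it. This stands, but that model is secondary, and the centre and Hoehn & Yahr models are exploratory. None of them supplies the primary estimate.

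Third, planned power is met without adjustment, and omitting the stratifiers causes neither bias nor an inflated type I error. This also stands.

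Fourth, a statistical analysis plan is promised and could add covariates. But the article does not leave the fixed factors open. It lists them and assigns the stratifiers to other models, so an analysis plan that follows it would carry the mismatch forward.

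**Conclusion.** The mismatch between design and analysis is certain from the text: three factors govern the randomisation and none is in the primary model. Its consequence is conditional. The stated analysis is valid and, if anything, conservative, and it should not be described as underpowered or wrong.

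Precision is forgone in two situations. One is that the stratifiers predict change in dual-task gait velocity, which the article's remarks on learning make plausible for FOG. The other is that the contrast turns out to be a between-arm difference in level at one session, which the wording does not exclude. The size is unknown: an SE ratio between 1.00 and 0.894 for an assumed R² of 0 to 20%, with a power gain of zero to about 6 percentage points. This is a worthwhile improvement at negligible cost, not a defect that threatens the trial's conclusion.

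**What to change.** Before unblinding, add centre, FOG stratum and Hoehn & Yahr stratum to the primary model as fixed effects, each with its interaction with session, and do the same in the secondary models analysed in a similar way. The session interactions are essential, since main effects alone leave a change contrast untouched. Use the values recorded at randomisation; this matters for FOG because the New FOGQ is repeated at all four sessions. Name the contrast that gives the treatment effect, so that it is clear whether change or level is compared. Keep the treatment-by-factor terms and the FOG three-way model as separate analyses with their present secondary or exploratory status.

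The cost is a short addition to the analysis plan and about 12 fixed-effect parameters in 120 patients. In the simulated change analysis the cost at R² = 0 was negligible (SE ratio 1.001, same power).

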### Sample size

Primary outcome is DT gait velocity. Single task gait velocity changes of around 0.05 m/s have been found clinically meaningful [38] but no such data presently exist for dual task gait velocity. Sample size power calculation [56] was based on data from the RESCUE trial in which in a similar study population had a mean dual task gait speed of 0.77 m/s (SD = 0.21) [38,57]. Power was set at 80% and based on two-sided 95% confidence intervals. We assumed that there would be a difference of 15% between both arms in favor of IDT based on previous study [51]. In analogy to the RESCUE study, in which a home-based intervention was delivered, a drop-out rate of 5% was envisaged. Assuming a stable control period, we calculated our sample size to include a total of 108 subjects (54 per center). Incorporating a loss to follow-up, we will aim to recruit 60 patients (total of 120 subjects) per group over a period of two years.

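### A random subject factor is the only dependence term stated for the primary mixed model; used with independent residuals it gives every session contrast one standard error and probably makes the 12-week interval too narrow

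*Protocol article*

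**What the plan says.** Under Data analysis/statistics, the protocol article states that "the DT walking performance at test session 1, 2, 3 and 4 will be evaluated using a linear mixed model". It then lists the model terms: "The fixed factors will be treatment (IDT vs. CTT), test session (1, 2, 3 and 4) and the interaction between test session and treatment group", followed by "Subject will be a random factor". No residual covariance is named. The treatment difference is to come from an appropriate contrast of session means, without saying which sessions, and secondary endpoints follow the same approach. The section also sets the level ("Tests will be two-sided with α 0.05") and promises more detail later: "A statistical analysis plan will be developed prior to unblinding and analysis".

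The Abstract and the Study design section fix the timing: a six-week control period, six weeks of training and a 12-week follow-up. The sessions therefore fall at weeks 0, 6, 12 and 24, with training between sessions 2 and 3.

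**The concern.** A random subject intercept with independent, equal-variance residuals is compound symmetry: one variance, and one correlation for all six session pairs. Sessions 1 and 2, six untreated weeks apart, are then taken to be as alike as sessions 1 and 4, which are 24 weeks apart with training in between.

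The protocol's own reasoning makes this doubtful. It expects response to training to differ by freezing status and cognition, and patient-level differences in response change the variances and correlations after training.

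At stake are the standard errors, confidence intervals and p-values of the treatment contrasts. The 12-week contrast matters most, because the hypothesis about consolidation and retention rests on it.

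**Working it through.** **The plan's own figure.** The Sample size section uses a "mean dual task gait speed of 0.77 m/s (SD = 0.21" m/s), a 15% difference and 80% power. The difference is 0.15 × 0.77 = 0.1155 m/s. Then n = 2 × (0.21/0.1155)² × (1.960 + 0.842)² = 51.9, so 52 per arm; the t-based version gives 53 per arm (106 in total). With the difference rounded to 0.115 m/s, the t-based version gives 54 per arm, the stated 108. This calculation uses no between-session correlation, so the present point does not touch it.

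**Inputs.** Sessions at weeks 0, 6, 12 and 24, and SD 0.21 m/s, are from the article. For standard errors in m/s I use 57 per arm (60 × 0.95, the stated 5% drop-out). All correlations are assumptions. The contrast is not tied to sessions, so I take 4 vs 2 (12-week follow-up) and 3 vs 2 (after training), with session 2 as the last assessment before training.

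**Formula.** With complete data, the random-intercept model gives every pairwise change the average of the six true change variances. For a given contrast:

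- ratio = √(average change variance / true change variance);
- actual size = 2Φ(−1.96 × ratio).

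An interval is too narrow exactly when that contrast's change variance is above the average.

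**Mild decay, worked.** Let the correlation fall linearly from 0.85 at 6 weeks to 0.80 at 24 weeks. In units of SD², the change variances 2(1 − ρ) are:

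- 0.300 (1–2) and 0.300 (2–3);
- 0.333 (1–3) and 0.333 (3–4);
- 0.367 (2–4);
- 0.400 (1–4).

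The average is 2.033/6 = 0.339.

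- 4 vs 2: √(0.339/0.367) = 0.961, size 6.0%. The modelled SE is 0.21 × √(2 × 0.339/57) = 0.0229 m/s; the true SE is 0.0238.
- 3 vs 2: √(0.339/0.300) = 1.063, size 3.7%.

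**Training break, worked.** Take 0.90 within the pre-training and post-training pairs and 0.80 across. The change variances are 0.2 twice and 0.4 four times, averaging 0.333. Both contrasts have ratio √(0.333/0.4) = 0.913, size 7.4%.

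**Variable response, worked.** Take correlation 0.80 plus extra variance v, a fraction of the baseline variance, shared by sessions 3 and 4. The across-training change variance is 0.4 + v and the average is 0.4 + 4v/6. With v = 0.05 the ratio is √(0.4333/0.45) = 0.981; with v = 0.20 it is √(0.5333/0.60) = 0.943.

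| Assumed pattern | 4 vs 2: ratio, size | 3 vs 2: ratio, size |
|---|---|---|
| Equal, 0.80 | 1.000, 5.0% | 1.000, 5.0% |
| Equal 0.80, SD 0.21/0.21/0.23/0.24 | 0.980, 5.5% | 1.013, 4.7% |
| Linear 0.85 to 0.80 | 0.961, 6.0% | 1.063, 3.7% |
| Linear 0.85 to 0.70 | 0.913, 7.4% | 1.179, 2.1% |
| Exponential, 0.70 at 6 weeks | 0.878, 8.5% | 1.299, 1.1% |
| Exponential, 0.90 at 6 weeks | 0.857, 9.3% | 1.411, 0.6% |
| Exponential, 0.95, same rising SDs | 0.843, 9.8% | 1.441, 0.5% |
| Training break 0.90/0.80 | 0.913, 7.4% | 0.913, 7.4% |
| Variable response, v = 0.05 | 0.981, 5.4% | 0.981, 5.4% |
| Variable response, v = 0.20 | 0.943, 6.5% | 0.943, 6.5% |

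**The case against.** The strongest reply is that the article does not exclude a structured residual. Naming subject as random identifies the clustering unit, and the residual covariance is ordinary analysis-plan content, which the article defers to a plan still to be written. A reader might infer that the protocol forces compound symmetry; it does not. This part stands, and silence alone would be no finding. But the section is not silent: it lists the model's terms and names one dependence term. An analysis plan that follows it literally inherits the assumption.

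Second, everything quantitative rests on assumed correlations, and mild cases are plausible. A stable patient trait plus measurement error plus a small decaying part gives only about 5.3% to 6.0% for session 4 vs 2 and 3.6% to 4.6% for session 3 vs 2. This stands too, and is why the result is given as a range starting close to 5%.

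Third, the consequence is bounded. With complete data only the standard errors change. Planned drop-out is 5%, and sensitivity analyses for missing values are promised. With missing sessions the assumed covariance also enters the estimates, but I have no basis for calling that effect large.

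**Conclusion.** The point holds in a limited form. As written and with independent residuals, the model gives one standard error to all between-session changes, in a design with unequal gaps and training in the middle. For session 4 vs 2 the size is 5.0% under equal variances and correlations, and about 5.4% to 9.8% under the other patterns tabulated, so the 12-week interval is likely to be too narrow. The upper end needs steep decay; about 6% is the figure for mild decay.

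Two stronger readings are tempting and unsupported. One is that the post-training and 12-week tests err in opposite directions. That holds under decay, but under a training break or variable response both are anti-conservative. The other is a size of 12% to 16%. That belongs to session 4 against the mean of sessions 1 and 2, a contrast the article does not name, and it needs steep decay. Treatment estimates from complete data and the sample size are unaffected.

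**What to change.** Replace the random subject intercept with an unstructured 4x4 within-subject covariance over the four sessions, keeping the stated fixed effects. It should replace the intercept rather than be added to it, because the unstructured matrix already contains any shared subject variance. Name heterogeneous Toeplitz as the fallback if the model does not converge. It is second best here because it ties correlations to session order rather than weeks, so pairs 1–2 and 3–4 share one despite gaps of 6 and 12 weeks. Use the same structure for the continuous secondary endpoints.

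The change is one or two sentences, settled before unblinding. It uses ten covariance parameters (four variances and six covariances) instead of two, a negligible loss with about 120 patients. If correlations really are equal, almost nothing is given up.

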**Methods and design:**

Hundred and twenty patients with Parkinson’s disease will be recruited to participate in this multi-centered, single blind, randomized controlled trial. Patients in Hoehn & Yahr stage II-III, with or without freezing of gait, and who report dual task difficulties will be included. All patients will undergo a six-week control period without intervention after which they will be randomized to integrated or consecutive task practice. Training will consist of standardized walking and cognitive exercises delivered at home four times a week during six weeks. Treatment is guided by a physiotherapist twice a week and consists of two sessions of self-practice using an MP3 player. Blinded testers will assess patients before and after the control period, after the intervention period and after a 12-week follow-up period. The primary outcome measure is dual task gait velocity, i.e. walking combined with a novel untrained cognitive task to evaluate the consolidation of learning. Secondary outcomes include several single and dual task gait and cognitive measures, functional outcomes and a quality of life scale. Falling will be recorded as a possible adverse event using a weekly phone call for the entire study period.

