Therefore, the primary aim of this study is to compare the effectiveness of consecutive versus integrated training (tested by combining walking with cognitive exercises) on DT gait performance in PD. We hypothesize that IDT practice will resort in better dual task outcomes and better consolidated learning results, particularly in patients without cognitive impairment. As secondary questions we will examine which dual task training mode is most beneficial in terms of fall risk reduction and leads to the best dual task gains in freezers versus non-freezers. Here, we describe the design of this training study, also referred to as the DUALITY trial.

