## Methods/design

### Study design and setting

The study has a parallel group design and involves a dual-centered, single blind, randomized controlled trial with a 12 week follow-up period. The study will include 120 patients with PD of Hoehn & Yahr stage II to III [53]. Individuals with PD will be randomly allocated to two arms: (a) six weeks of integrated dual task training (IDT); or (b) six weeks of consecutive task training (CTT). Both interventions will be delivered at the patient’s home with the same frequency and intensity: 12 supervised sessions by a physiotherapist and 12 unsupervised training sessions. Preceding the intervention, participants will undergo a six week control period without training to ascertain the effect of repeated measures (Figure 1). All other interventions (medication, allied health care) will be kept as stable as possible. Any changes in treatment or medication will be monitored. The trial will be conducted in two countries. Sixty patients will be recruited at the Radboud University Medical Center (RUMC) in the Netherlands and sixty patients will be recruited at the University Hospitals in Belgium.

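### The fall analysis leaves the count model to the observed data and states no use of the control-period falls, recorded before randomisation, as a baseline covariate

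*Protocol article*

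**What the plan says.** The whole analysis of falls is one sentence in the Data analysis/statistics section: "Fall frequency data will be analyzed using a negative binomial model depending on the distribution of the data". The same section promises a statistical analysis plan before unblinding.

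On data collection, the Falls monitoring section says "For the entire study period of 24 weeks, the patient will receive a weekly phone call". On timing, the abstract says "All patients will undergo a six-week control period without intervention after which they will be randomized to integrated or consecutive task practice". The purpose given for that period, under Study design and setting, is that "participants will undergo a six week control period without training to ascertain the effect of repeated measures"; no use is stated for the falls recorded in it.

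The status of falls varies. The Background says "As secondary questions we will examine which dual task training mode is most beneficial in terms of fall risk reduction", while Table 3 lists the number of falls among the tertiary outcomes, as an adverse effect. The Sample size section concerns dual task gait velocity only.

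**The concern.** Two things about the sentence deserve attention.

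First, the model is made conditional on how the data turn out, with no criterion and no named alternative. Falls in Parkinson's disease differ greatly between patients: the Background reports that about 60% fall each year and about two thirds fall recurrently, and the Falls monitoring section itself calls falling very variable. If the choice fell on a model that ignores this spread, the standard error would be too small and the type I error too high. An open choice also allows selection among results.

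Second, every patient contributes six weeks of falls before randomisation, counted by the same calls that count falls afterwards. That count predicts a patient's later falls and cannot be affected by arm. The stated analysis does not mention it, so differences between patients that it could explain would stay in the error term.

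At stake is the precision and validity of the comparison on fall risk, which is a stated secondary question and part of the safety evidence.

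**Working it through.** **Timeline.** The control period is 6 weeks, training 6 weeks and follow-up 12 weeks: 6 + 6 + 12 = 24, which reproduces the article's recording period. Randomisation comes after week 6, so 18 of the 24 weeks follow it and 6/24 = 25% precede it.

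**Inputs.** The article gives no weekly fall rate, dispersion or fall effect. The following are assumptions: 0.05 to 0.15 falls per patient-week, gamma-distributed patient rates with variance k = 1 to 2, and a rate ratio of 0.6. From the article come the two-sided 5% level and 57 patients per arm (60 × 0.95, using its 5% drop-out).

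**Precision without the covariate.** For the 18 weeks after randomisation, the mean counts are m0 = 18 × rate and m1 = 0.6 × m0. The variance of the log rate ratio is (1/m0 + 1/m1 + 2k)/57. At rate 0.05 and k = 1 this is (1.111 + 1.852 + 2)/57 = 0.0871, so SE = 0.295. Then |ln 0.6|/SE = 0.511/0.295 = 1.73, and power is Φ(1.73 − 1.96) = 41%. At rate 0.15 and k = 2 it is (0.370 + 0.617 + 4)/57 = 0.0875, so SE = 0.296 and power is again about 41%. The simulation below gives 42% in both cases.

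**Model choice.** If a Poisson model is fitted to such counts under no effect, the true variance exceeds the assumed one by the factor 1 + k·m0. At rate 0.15 and k = 2 this is 1 + 2 × 2.7 = 6.4. The chance of rejection is then P(|Z| > 1.96/√6.4) = P(|Z| > 0.775) = 44%. At rate 0.05 and k = 1 the factor is 1.9, which gives about 16%.

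**Simulation** (gamma-Poisson counts, 400 replicates per setting, 18 weeks after randomisation, covariate based on the control-period count):

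| Falls/week | k | Power, unadjusted | Power, adjusted | Gain (points) | Null rejection, Poisson | Null rejection, negative binomial (unadjusted / adjusted) |
|---|---|---|---|---|---|---|
| 0.05 | 1 | 42.2% | 47.0% | 4.8 | 18.5% | 6.0% / 6.2% |
| 0.05 | 2 | 33.0% | 37.8% | 4.8 | 17.8% | 2.8% / 5.5% |
| 0.15 | 1 | 62.3% | 70.3% | 8.0 | 27.2% | 4.8% / 6.2% |
| 0.15 | 2 | 42.0% | 60.8% | 18.8 | 45.0% | 5.5% / 7.5% |

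Monte Carlo error is about 2.5 points per power estimate. A separate simulation under the same assumptions gave power of 34 to 66% rising to 38 to 78%, a standard error about 4 to 23% smaller, and Poisson rejection of a true null in 20 to 45% of runs. Across the simulations the gain in power is about 2 to 21 points.

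**Cross-check of the gain.** A 23% cut at rate 0.15 and k = 2 takes the SE from 0.296 to 0.296 × 0.77 = 0.228. Then 0.511/0.228 = 2.24 and power is Φ(0.28) = 61%, in line with the table. A 4% cut at rate 0.05 and k = 1 gives SE 0.283 and power of about 44%, a gain of 3 points.

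**Why the range is wide.** The share of patients with no control-period fall is (1 + k × 6 × rate)^(−1/k). It is 1/1.3 = 77% at rate 0.05 and k = 1, and 1/√2.8 = 60% at rate 0.15 and k = 2. When falls are rare, the six-week count separates patients less well.

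**Conditional case only.** If all 24 weeks were counted, the apparent rate ratio would be (6 + 18 × RR)/24. For RR = 0.60 this is (6 + 10.8)/24 = 0.70, and ln 0.70/ln 0.60 = 0.357/0.511 = 0.70, so about 30% of the log rate ratio would be lost.

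**The case against.** The strongest objection is that the article is a condensed account and defers to a later analysis plan. A counting window, an exposure offset and covariates are the sort of detail usually settled there, so their absence is not in itself an error. That stands for the window and the offset.

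A reader might go further and infer that the arms will be compared on the 24-week count, so that pre-randomisation falls dilute the effect. The documents do not support this. The 24-week sentence describes data collection, and weekly records allow any window. The article treats the control period as a separate phase, and the session factor in its gait model keeps it apart. Nor may one infer that the control-period falls will be discarded: the article is silent, and it also collects retrospective falls over the past year, another possible baseline measure.

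It might also be inferred that the open model choice dilutes the effect or loses power. It does neither; its risk is to type I error. The article does not name Poisson as the alternative, so that risk too is conditional on what would be chosen.

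Finally, falls are listed as a tertiary outcome, the trial was not sized for them, and every fall rate used here is assumed. All of this stands and limits the weight of the point. It does not remove it: the wording on model choice is an affirmative statement, not an omission, and a more precise analysis is available from data already being collected.

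**Conclusion.** The point holds in a limited form. The stated analysis lets the observed distribution decide the model without a rule, and it states no use of a baseline count that the trial collects anyway. Under 0.05 to 0.15 falls per week, between-patient variance of 1 to 2 and 57 patients per arm, fixing the negative binomial model avoids a choice that could reject a true null in roughly 18 to 45% of trials. Adjusting for control-period falls shortens the standard error by about 4 to 23% and adds about 2 to 21 points of power at a rate ratio of 0.6. At low fall rates the gain is small. The adjusted model's own null rejection was 5.5 to 7.5% in the tabulated simulation, so a little of the gain may reflect a slightly liberal test.

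The shrinkage from 0.60 to 0.70 applies if, and only if, all 24 weeks were counted, which the article does not say. Even after the change, power for falls stays below 80% at this rate ratio and these assumptions. Confidence is moderate, because the size rests on assumed rates and the analysis plan may already settle the details.

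**What to change.** Before unblinding, replace the conditional sentence with a commitment. Compare falls from randomisation to week 24 using a negative binomial model fixed in advance, with log(weeks observed) as offset. Include arm, the randomisation strata and the control-period fall count, for example as log(count + 0.5). Name in advance what will be done if the model does not converge.

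The cost is a few sentences in the analysis plan. No new data, visits or patients are needed. The comparison counts 18 weeks of falls, and the 6 weeks before randomisation serve as baseline, where they carry information about the patient but none about treatment.
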